# Intravenous magnesium sulfate for the management of severe hand, foot, and mouth disease with autonomic nervous system dysregulation in Vietnamese children: study protocol for a randomized controlled trial

**DOI:** 10.1186/s13063-016-1215-6

**Published:** 2016-02-19

**Keywords:** Hand, foot, and mouth disease, brainstem encephalitis, magnesium sulfate, randomized controlled trial

## Abstract

**Background:**

Over the last 15 years, hand, foot, and mouth disease (HFMD) has emerged as a major public health burden across the Asia-Pacific region. A small proportion of HFMD patients, typically those infected with enterovirus 71 (EV71), develop brainstem encephalitis with autonomic nervous system (ANS) dysregulation and may progress rapidly to cardiopulmonary failure and death. Although milrinone has been reported to control hypertension and support myocardial function in two small studies, in practice, a number of children still deteriorate despite this treatment. Magnesium sulfate (MgSO_4_) is a cheap, safe, and readily available medication that is effective in managing tetanus-associated ANS dysregulation and has shown promise when used empirically in EV71-confirmed severe HFMD cases.

**Methods/Design:**

We describe the protocol for a randomized, placebo-controlled, double-blind trial of intravenous MgSO_4_ in Vietnamese children diagnosed clinically with HFMD plus ANS dysregulation with systemic hypertension. A loading dose of MgSO_4_ or identical placebo is given over 20 min followed by a maintenance infusion for 72 h according to response, aiming for Mg levels two to three times the normal level in the treatment arm. The primary endpoint is a composite of disease progression within 72 h defined as follows: development of pre-specified blood pressure criteria necessitating the addition of milrinone, the need for ventilation, shock, or death. Secondary endpoints comprise these parameters singly, plus other clinical endpoints including the following: requirement for other inotropic agents; duration of hospitalization; presence of neurological sequelae at discharge in survivors; and neurodevelopmental status assessed 6 months after discharge. The number and severity of adverse events observed in the two treatment arms will also be compared. Based on preliminary data from a case series, and allowing for some losses, 190 patients (95 in each arm) will allow detection of a 50 % reduction in disease progression with 90 % power at a two-sided 5 % significance level.

**Discussion:**

Given the large numbers of HFMD cases currently being seen in hospitals in Asia, if MgSO_4_ is shown to be effective in controlling ANS dysregulation and preventing severe HFMD complications, this finding would be important to pediatric care throughout the region.

**Trial registration:**

ClinicalTrials.gov Identifier: NCT01940250 (Registered 22 August 2013).

**Electronic supplementary material:**

The online version of this article (doi:10.1186/s13063-016-1215-6) contains supplementary material, which is available to authorized users.

## Background

Hand, foot, and mouth disease (HFMD) is a common infectious disease, primarily affecting young children, caused by a number of enteroviruses belonging to the species *Human enterovirus A* and including coxsackievirus a16 (CA16) and enterovirus 71 (EV71). Infection with EV71 is of particular concern because it can cause severe HFMD, sometimes resulting in death. Over the past 15 years, EV71-associated HFMD has emerged across Asia, with outbreaks thought to involve millions of people occurring in the region [1]. EV71-related HFMD has also increased markedly in Vietnam during this period, and in 2011, 170 deaths occurred among the 113,000 Vietnamese children clinically diagnosed with the disease [2].

### Autonomic nervous system (ANS) dysregulation and HFMD

During outbreaks, thousands of children can develop HFMD, and although most will have self-limited illness with fever and rash only, a small proportion will develop neurological and systemic complications that can be rapidly fatal. Neurological manifestations of EV71 infection include aseptic meningitis and acute flaccid paralysis, but the issue of most concern is brainstem encephalitis because autonomic nervous system (ANS) dysregulation may occur, potentially with rapid progression to cardiopulmonary failure [1]. Clinical features indicating ANS dysregulation include high persistent fever, profuse sweating, mottled skin, tachycardia, tachypnoea, hypertension, and hyperglycemia [3]. The Vietnamese Ministry of Health (MoH) has developed guidelines for clinical staging and suggested management of HFMD, according to the severity grade (Additional file 1: Appendix 1). Briefly, Grade 1 represents classic HFMD without complications. Patients with Grade 2 disease show some evidence of central nervous system involvement, usually manifesting as myoclonus. In Grade 3 disease, evidence of ANS dysfunction is present, whereas patients with Grade 4 disease have cardio-pulmonary compromise.

Although the mechanisms underlying the ANS dysregulation have not been clearly defined, evidence exists that inflammation occurs in the medulla oblongata and cervical spinal cord, causing increased sympathetic activity and resulting in severe systemic and pulmonary hypertension and eventually pulmonary edema [1]. The frequency of ANS dysregulation is also unclear because many of the signs are rather subjective and also can be present among children with high fever; however, the development of systemic hypertension in children with HFMD is considered to be unequivocal evidence of ANS dysregulation. The frequency with which this occurs is not known, however, because only severe cases are usually reported. In one study of 36 severe EV71 infection cases from Taiwan, more than 36 % developed systemic hypertension, whereas in 22 severe HFMD cases reported from China, 17 cases had hypertension [4].

Research has also revealed left ventricular dysfunction in patients with EV71-associated brainstem encephalitis/hypertension who later develop pulmonary edema. Although no histological or virological evidence of viral myocarditis was seen, catecholamine-associated cardiotoxic effects were found on histological examination of cardiac ventricular biopsies, together with high concentrations of norepinephrine and epinephrine in plasma from these patients [5]. Thus, high plasma catecholamine concentrations secondary to brainstem encephalitis are purported to have a direct effect on cardiac function, as well as to cause pulmonary edema by raising pulmonary pressures [1]. Alternatively, or in addition, the impact of altered cytokine profiles on the cardiopulmonary system may influence the severity of HFMD [6]. In small studies, the severity of EV71 infection has been associated with altered concentrations of a number of different cytokines, including TNF∝, INFγ, IL6, and IL13, in blood and cerebrospinal fluid (CSF), with evidence that cytokine levels correlate with the degree of injury to the brainstem and spinal ganglia [7]. Moreover, in a number of animal studies of neurogenic hypertension, associations have been demonstrated between inflammatory cytokine levels and enhanced vasomotor and cardiac sympathetic drive [8].

### Management of ANS dysregulation

Management of ANS dysregulation presents particular challenges. In one report from Taiwan, use of the phosphodiesterase-3 inhibitor, milrinone was said to control hypertension and support myocardial function in a group of 24 children with severe HFMD compared to historical controls [9]. In addition, milrinone was shown to decrease mortality in HFMD patients with pulmonary edema in a small, open-label, randomized clinical trial in Vietnam [10]. On the basis of these small studies, milrinone has now become the recommended therapy for HFMD with ANS dysregulation in Vietnam, with MoH guidelines setting down indications for when the drug should be commenced in suspected HFMD cases. Currently, the MoH guidelines define the intervention level for use of milrinone to be when the systolic blood pressure (SBP) exceeds the 99th percentile for age plus 5 mmHg, which approximates to the internationally accepted definition of Stage 2 hypertension in children (Additional file 1: Appendix 1) [11]. However, clinical failures still occur despite high dose intravenous milrinone, and a number of children go on to require hemofiltration and ventilatory support, the next steps recommended in the Vietnamese MoH guidelines (Additional file 1: Appendix 2). Secondly, there are few clinical or safety data available with respect to milrinone use in children, apart from a few small studies following cardiac surgery [12] [13]. Recent reports suggest that milrinone use is an independent risk factor for clinically significant tachyarrhythmia after congenital heart surgery, and may be associated with development of acute renal failure [13].

### Magnesium sulfate and ANS dysregulation

Autonomic disinhibition is also postulated to occur in severe tetanus. Elevated concentrations of circulating catecholamines have been observed, and urinary epinephrine and norepinephrine excretion are increased proportional to disease severity [14, 15]. In a randomized controlled trial comparing magnesium sulfate (MgSO_4_) with placebo in patients with severe tetanus, the use of magnesium was associated with significantly reduced requirements for drugs to control muscle spasms and cardiovascular instability [16]. In patients undergoing tracheal intubation or surgery for pheochromocytoma, the use of magnesium was associated with a reduction in SBP and in plasma catecholamine concentrations [17]. Isolated reports exist of rapid and effective control of life-threatening autonomic hyperreflexia in patients with spinal cord lesions [18–22]. In in vitro studies, magnesium has been shown to reduce catecholamine secretion from the peripheral nerve endings and the adrenal medulla [23]. Intrapartum use of MgSO_4_ in women with preeclampsia was associated with reduced cytokine levels in the women and their babies [24]. Similarly, the use of magnesium in a small number of patients with aneurysmal subarachnoid hemorrhage was associated with reduced serum levels of certain inflammatory cytokines [25]. Formal safety data relating to the use of MgSO_4_ in pediatric care are limited, but from its use in children with severe asthma [18] and in a small number of neonates with uncontrolled pulmonary hypertension [26], adverse effects appear to be infrequent.

In summary, although HFMD has become one of the major contributors to childhood morbidity and mortality in Vietnam, current management strategies rely on guidelines that are based on expert opinion and only two small clinical studies. Vietnamese MoH guidelines currently indicate that milrinone should be used when Stage 2 hypertension develops, but evidence for the efficacy of this intervention is limited, and a number of children (approximately 20 %, personal communication [name] [name]) treated in this way require additional interventions. In addition, milrinone is an expensive drug with a known toxicity profile and requires highly experienced staff to administer it. We hypothesized that early intervention with MgSO_4_ in Grade 3 HFMD, when Stage 1 hypertension and ANS dysregulation first become apparent, might control cardiovascular instability more effectively and prevent progression to more severe disease. MgSO_4_ is cheap, readily available, and generally considered to be safe. Given the very large numbers of HFMD cases currently being seen in hospitals in Asia, if MgSO_4_ is shown to be effective in controlling ANS dysregulation and preventing severe HFMD complications, this finding would be important to pediatric care throughout the Asian region.

#### Primary objective of the trial

The primary objective of the trial is to evaluate the effects of MgSO_4_ for the control of hypertension and progression to severe disease (shock, respiratory compromise, or death) in children with severe HFMD and ANS dysregulation.

#### Secondary objectives of the trial

The secondary objectives of the trial are as follows:To describe the clinical signs of autonomic dysfunction observed in children with severe HFMD; measure levels of biomarkers of sympathetic activity, including plasma and urine catecholamine levels and levels of inflammatory cytokines; and to assess the impact of MgSO_4_ on these parameters.To examine the relations between measures of cardiac output (CO) and systemic vascular resistance (SVR) with clinical signs of autonomic dysfunction and to assess the impact of MgSO4 on these parameters.To evaluate the effects of MgSO_4_ on long-term outcome from severe HFMD in survivors, by assessing neurodevelopmental status at 6 months.

## Methods/Design

### Study Design

This is a randomized, placebo-controlled, double-blind trial to assess the efficacy and side effect profile of intravenous MgSO_4_ when used in Vietnamese children with clinically diagnosed HFMD and signs of ANS dysregulation with systemic hypertension.

### Study sites

The Hospital for Tropical Diseases (HTD) and Children’s Hospital Number One (CH1) are two major hospitals in Ho Chi Minh City, Vietnam, with 1600 in-patient beds in total. Each hospital functions as a first-level facility for the immediate local population and as a tertiary referral center responsible for the diagnosis and management of serious infectious diseases for a population of over 15 million children across southern Vietnam. The Oxford University Clinical Research Unit (OUCRU) is located on the HTD site, and together, the three institutions have established a number of fruitful research collaborations over more than 20 years.

### Inclusion and exclusion criteria (see Additional file 1: Appendices 1-4 for definitions/additional details)

Vietnamese MoH guidelines indicate that all suspected HFMD cases with Grade 2 or more severe disease should be admitted to a Pediatric Intensive Care Unit (PICU) or High Dependency Unit (HDU) facility for close observation. The guidelines also indicate that a peripheral arterial line should be inserted for invasive BP monitoring if there are any signs of ANS dysfunction. For patients with Grade 3 disease (that is, the group eligible for inclusion in this study), the pulse, BP, respiratory rate and pattern, oxygen saturation, and temperature must be monitored very closely, and the child should receive intravenous sedation with phenobarbitone, as well as a dose of 1 g/kg intravenous immunoglobulin (IVIG) as soon as possible, with a second dose of IVIG 24 h later.

All patients aged 6 months to 15 years admitted to the PICU at HTD or the HDU on the Infectious Diseases Ward at CH1 in Ho Chi Minh City with clinically suspected HFMD (Additional file 1: Appendix 1) are considered for eligibility for this trial. Patients are eligible for enrollment if a) the arterial blood pressure (BP), measured via an indwelling catheter, exceeds the internationally recognized definition for Stage 1 hypertension in children (Additional file 1: Appendix 3) [27]; b) they exhibit at least one other criterion for ANS dysregulation (Additional file 1: Appendix 4), such as tachypnea for age, irregular or labored breathing but with oxygen saturation above 92 % in air and a normal arterial blood gas, resting heart rate sustained above 150 beats/minute, mottled skin, profuse sweating, refractory fever, or hyperglycemia; and c) no contraindications to study inclusion are present, including a past history of hypertension, chronic renal, cardiac or pulmonary disease, or any neurological disorder; features indicating a current hypertensive emergency (see below); treatment with milrinone or any other inotropic agent has already commenced; respiratory distress is present with oxygen saturation below 92 % in air or an arterial pCO_2_ over 45 mmHg; atrioventricular block or any arrhythmia (other than sinus tachycardia) is present on an ECG rhythm strip, or the QT interval is prolonged; or reduced urine output or increased creatinine levels indicate renal compromise. If the patient fulfils these criteria and a parent or guardian gives written informed consent (see “Ethical Considerations” section), then the child is enrolled in the study.

The current Vietnamese MoH guidelines specify that milrinone should be given to children with HFMD and ANS dysregulation when the SBP is sustained at a level exceeding a value approximating the 99th percentile for age plus 5 mmHg (that is, Stage 2 hypertension) with the intention that treatment should commence within 1 to 2 h [28]. Enrollment to this study is designed to be early, when hypertension is first identified (at Stage 1), so that in the event of treatment failure, the MoH treatment guidelines can be applied. A small number of patients who present with Stage 2 hypertension may also be enrolled; in such cases, very stringent BP criteria will ensure that, if the BP does not improve within 30 min of commencing the study drug, milrinone will be added. That is, all Stage 2 patients will be on milrinone within 1 h of presentation unless the BP falls to Stage 1 levels.

### Intervention / study medication

Detailed information on the use of MgSO_4_, the pharmacokinetics, the side effects profile, etc. is provided in Additional file 1: Appendix 5. Patients are assigned to one of two treatment arms and follow the same dosing schedule in both arms. After written informed consent has been obtained, staff administer a loading dose of 50 mg/kg of either MgSO_4_ or a visually matched placebo (sterile water) by continuous infusion into a peripheral intravenous line over 20 min, followed by a maintenance infusion in the treatment arm of 30 to 50 mg/kg/h for 72 h according to response, aiming for plasma Mg levels two to three times the normal level. All staff members involved in the clinical care remain blind to the treatment allocation, and Mg levels are monitored and adjusted by independent doctors from another clinical facility as detailed in the section on “dose adjustment” below.

### Study endpoints

*The primary endpoint* is a composite endpoint indicating disease progression within 72 h. It is defined as the occurrence of any of the following within 72 h of commencing the study drug infusion:Specific BP criteria necessitating the addition of milrinone as detailed in the section “Criteria for the addition of milrinone” below.Need for mechanical ventilation.Development of shock.Death.

*Secondary endpoints* comprise these parameters singly, plus a number of other clinical endpoints including the following: a requirement for other inotropic agents (for example, dobutamine), duration of hospitalization, presence of neurological sequelae at discharge in survivors, and neurodevelopmental status assessed 6 months after discharge.

*Safety endpoints* include the number of adverse events (AEs) and severe adverse events (SAEs) that occur in the two treatment arms.

*Exploratory endpoints* will be assessed, including serial measurements of cardiac output (CO) and systemic vascular resistance (SVR), catecholamine levels, and cytokine levels. We will assess the impact of MgSO_4_ on these parameters, provided the data collected appear reliable and consistent within individual participants.

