Magnesium is an important cofactor in many enzymatic reactions in the body, but the side effect profile is well known, and in the dose range used here, it is generally considered safe (Additional file 1: Appendix 5). However, differentiation between potential magnesium toxicity and progression of HFMD can be difficult. All staff involved in the study have been trained to recognize potential side effects, and a series of standard operating procedures have been put in place indicating when to stop study treatment and/or initiate rescue therapy if any complications occur that might be related to the treatment (Additional file 1: Appendix 6). Similarly, all staff members are aware that they may request an urgent Mg/Ca level at any time or request emergency unblinding in the case of any adverse event when knowledge of the identity of the study treatment might contribute to the treating physician’s ability to care for the patient.

Patients are assessed daily for the duration of the hospital stay. At discharge, full neurological and neurodevelopmental assessments are performed. Patients who have not recovered fully from the effects of sedation with phenobarbitone by the time of discharge, but are otherwise considered fit to go home, are asked to attend 1 week later for formal review and neurological assessment. All patients are also asked to return at 6 months post-enrollment for a clinical and neurodevelopmental assessment. After this, any further follow-up will be according to clinical need, and participants will be referred back to the standard hospital outpatient clinic system.

Neurodevelopmental assessments done at discharge (or 1 week later) and 6 months use the Bayley Scales of Infant Development, Third Edition (Bayley-III) and Movement ABC-2 tools. Children 36 months and under at enrollment will use the Bayley-III. Children 48 months and above at enrollment will use the Movement ABC-2 tool for their assessments.

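### Sequelae at discharge and 6-month neurodevelopmental status are defined in survivors only, so a child saved but impaired counts only against MgSO4 on these two secondary endpoints

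*Protocol article*

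**What the plan says.** The Study endpoints section of the protocol article includes among the secondary endpoints "duration of hospitalization, presence of neurological sequelae at discharge in survivors, and neurodevelopmental status assessed 6 months after discharge". The sequelae item is confined to survivors in that text. The 6-month item carries no survivor wording there. The Secondary objectives section supplies it: the aim is to evaluate the effect of MgSO4 on "long-term outcome from severe HFMD in survivors, by assessing neurodevelopmental status at 6 months".

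Death is counted elsewhere. It is one component of the primary composite, which is assessed "within 72 h of commencing the study drug infusion". The secondary endpoints "comprise these parameters singly, plus a number of other clinical endpoints", so death is also compared alone, most naturally over the same 72 h. Under Adverse Events, any death is a serious adverse event, and the number of these is a safety endpoint.

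The Statistical analysis section gives the type of regression for each kind of secondary endpoint and leaves the rest to an analysis plan that is not shown. It gives no place to a death in either neurological endpoint.

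**The concern.** Randomisation makes the two arms comparable at entry. It does not make the survivors of the two arms comparable if the drug affects who survives, and preventing death is part of the primary objective. Suppose MgSO4 keeps alive some very sick children who would have died on placebo, and they leave hospital with deficits. In the placebo arm such children are absent from both neurological endpoints. In the MgSO4 arm they are present and scored as bad outcomes.

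What is at stake is the long-term objective. Sequelae are read at discharge and development at 6 months, but the only listed efficacy endpoints that count death stop at 72 h. Over the longer window no listed efficacy endpoint credits MgSO4 with a death prevented after 72 h.

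**Working it through.** **Figures in the article.** None is given for these two endpoints. The planned size is 95 per arm. It rests on 85 per arm for 50% versus 25%, 90% power and two-sided 5%. That figure reproduces: the usual two-proportion formula gives 77 per arm, and 85 with the continuity correction. Only the 95 per arm is used below.

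**Mortality.** The article gives no rate for this population. Two figures bear on it:
- Trial status reports 0 deaths among 21 children, both arms pooled. The one-sided 95% upper limit is 1 − 0.05^(1/21) = 13.3%.
- Background gives 170 deaths in 113,000 clinical cases in 2011, which is 0.15%. This covers all grades of disease, not children with autonomic dysregulation.

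Control mortality m is therefore varied from 1% to 13.3%.

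**Assumptions not in the documents.** MgSO4 halves mortality, so MgSO4 mortality is m/2 and the proportion saved is m/2. Children who would survive on either arm have sequelae at rate s = 20%, unaffected by treatment. Every saved child has sequelae.

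**Formulas.**
- Sequelae in survivors, control: s.
- Sequelae in survivors, MgSO4: [(1 − m)s + m/2] / (1 − m/2).
- Death or sequelae, control: m + (1 − m)s.
- Death or sequelae, MgSO4: m/2 + (1 − m)s + m/2, which is the same.

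At m = 5%, the MgSO4 survivors show (0.95 × 0.20 + 0.025) / 0.975 = 0.215 / 0.975 = 22.1%. Death or sequelae is 0.05 + 0.19 = 24.0% in both arms.

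| Control mortality | Sequelae in survivors, control | Sequelae in survivors, MgSO4 | False excess (points) | Death or sequelae, each arm | Chance of significant apparent harm |
|---|---|---|---|---|---|
| 1% | 20.0% | 20.4% | 0.4 | 20.8% | about 3% |
| 5% | 20.0% | 22.1% | 2.1 | 24.0% | about 5% |
| 10% | 20.0% | 24.2% | 4.2 | 28.0% | about 10% |
| 13.3% | 20.0% | 25.7% | 5.7 | 30.6% | about 15% |

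The last column is the normal-approximation power at 95 per arm for a two-sided 5% test. Chance alone would give 2.5%. With no deaths the false excess is zero.

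**If not every saved child is impaired.** Let a fraction f of saved children have sequelae. The survivors-only difference is then (m/2)(f − s) / (1 − m/2), and death or sequelae differs by (m/2)(1 − f) in favour of MgSO4. At m = 5% and f = 50%:
- survivors only: 0.025 × 0.30 / 0.975 = 0.8 points against MgSO4;
- death or sequelae: 24.0% versus 22.75%, or 1.25 points for MgSO4.

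So the survivors-only comparison points the wrong way whenever saved children do worse than other survivors (f > s). The death-inclusive one does not.

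**The case against.** The strongest reply is that deaths are not lost from the trial. Death within 72 h is in the primary composite and is a secondary endpoint of its own, and every death is a serious adverse event compared between arms. A survival benefit would therefore be reported beside any excess of sequelae. This stands for the first 72 h. After that, deaths are visible only in the safety data.

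The second reply is that mortality looks low. With 0 of 21 deaths so far, the effect may be negligible. This also stands, and it limits the size of the point. It does not remove it, because 21 children are still compatible with mortality up to about 13%.

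The third reply is that such detail belongs in the analysis plan. That does not meet the point, because the restriction to survivors is stated in the article and a plan that follows it would inherit it.

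A reader might infer more than the documents support:
- **That "duration of hospitalization" rewards an early death with a short stay.** No text says so. Cox regression is provided for time-to-event endpoints, and a model that keeps deaths as never discharged fits the wording. How deaths enter this endpoint is commonly left to the analysis plan.
- **That the one-week deferral biases the sequelae endpoint.** It applies to "Patients who have not recovered fully from the effects of sedation with phenobarbitone by the time of discharge", and it prevents sedation being scored as deficit. Phenobarbitone is indicated for Grade 3 disease in both arms and outcome assessors are blinded. Adjusting for days to assessment would itself condition on something that happens after randomisation.
- **That averting 5 deaths per 95 produces 5/95 = 5.3 points of false harm.** This needs every death averted, every saved child impaired and no sequelae in anyone else. At 20% sequelae in other survivors the comparison is 18/90 = 20.0% versus 23/95 = 24.2%, or 4.2 points. If 5% mortality is only halved, it is about 2 points.

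**Conclusion.** The point holds for two secondary endpoints, sequelae at discharge and 6-month neurodevelopmental status. By the article's own wording both condition on survival, which MgSO4 may change, so neither is a fully randomised comparison if the arms differ in mortality. The direction of the bias is against MgSO4 when saved children are more often impaired than other survivors.

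Its size is zero without deaths and about 0.4, 2 and 4 points at 1%, 5% and 10% control mortality. Those figures rest on the assumed 20% sequelae rate, halved mortality and impairment in every saved child; milder assumptions give less. The primary analysis is unaffected. This is a worthwhile improvement to the secondary analyses, not a flaw that endangers the trial.

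**What to change.** Use as denominator the population already set for the primary analysis: all randomised children who commenced the loading dose, by randomised arm.

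- **At discharge:** analyse death or neurological sequelae as the endpoint.
- **At 6 months:** analyse neurodevelopmental status by ranks, with deaths by 6 months ranked worst. Ranking within each instrument avoids new impairment cut-offs across Bayley-III and Movement ABC-2.
- **Supportive:** keep the survivors-only results, labelled as such, and show deaths and deficits separately beside the combined results.

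Two details need settling for the 6-month analysis. Study endpoints times the assessment from discharge, while the follow-up section times it from enrolment; a child who dies in hospital is never discharged home, so one anchor must be named. The article also assigns no instrument to children older than 36 but younger than 48 months at enrolment, so their place in the ranking must be stated.

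The cost is wording in the protocol and analysis plan. Deaths and assessments are already collected, 21 of 190 children had been enrolled at the time of the article, and the analysis plan is to be finalised before unblinding. The drawback is that the discharge composite mixes death with deficit and gives no credit for a child who survives impaired. That is why the components must be shown with it.
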